### Statistical analysis

2.7.

First, a descriptive analysis (frequencies and percentages for categorical variables; and means and standard deviation for continuous variables) and a univariate analysis [one-way analysis of variance (ANOVA) for quantitative variables and the chi-square test for qualitative variables] will be used to examine the data and to test whether there are baseline differences between the groups after randomisation. Second, to answer the main objective—whether there are differences between treatment groups regarding their effectiveness in improving quality of life, linear mixed-effects models (LMEMs) (85) will be used. Cohen’s *d* will be calculated from the estimated mean values of SF-36 and its standard deviations (SD) at baseline (86). Moreover, LMEMs with the same aforementioned components will be used to analyse whether there are differences between the groups with respect to the improvement of the secondary variables.

The results from the trial will be presented as regression coefficients for predicting change in primary and secondary outcomes with 95% confidence intervals. LMEMs will be tested against a Bonferroni-adjusted alpha level of 0.01 (0.05/5) (87).

Data collection and statistical analysis will be performed by using Excel software, R statistical software (version 3.6.2) (88) and SPSS software (version 25.0) (89).

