In accordance with the results obtained in the literature (33), to detect a mean difference of 20 points on the physical scale of the 36-Item Short Form Health Survey Questionnaire (SF-36), with a standard deviation (SD) between the groups of 36.16, an alpha value of 0.05 and a power of 80%, 53 subjects per group will need to be recruited (106 subjects in total). We will increase this value by 10% to cover potential losses in the study, so the minimum sample required will be 116 subjects. Considering a mental scale, to detect a mean difference of 20 points, with an SD of 29.99 between the groups, an alpha value of 0.05 and a power of 80%, 35 subjects per group will need to be recruited (70 subjects in total). This number will be increased by 10% to counter possible losses, so the sample size is 77 subjects. Based on these calculations, the minimum sample required for the study will be 58 subjects per group (116 subjects in total). The sample size has been calculated using the Fisterra Guide for Determination of sample size (34). The formulae used have been added as Supplementary materials.

At the time of writing 90 participants (77.5% of the target sample size) have been recruited.

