### Randomisation, allocation and masking of the study groups

2.3.

Patients will be randomised once baseline data have been collected. Individual randomisation will be performed by an independent statistician using a computer-generated random number sequence with no restrictions. The sequence will be concealed throughout the study. Given the nature of the interventions, the patients will not be blind to their allocation. The information for the random allocation sequence will be implemented by phone by a research assistant (RA), who will state the type of treatment assigned for each new patient. The participants in the intervention group will be informed about what the intervention is and where and when they should carry it out. In addition, the RA will request that participants do not inform other researchers of their group allocation.

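### Section 2.7 handles baseline only by significance tests between randomised arms; it should drop them and state that each mixed model adjusts for the baseline score

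*Protocol article*

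**What the plan says.** Section 2.7 (Statistical analysis) starts with descriptive statistics, one-way ANOVA and chi-square tests, the tests being there "to test whether there are baseline differences between the groups after randomisation". It then names linear mixed-effects models (LMEMs) for quality of life and for the secondary variables, without listing fixed effects, covariates or the role of the baseline score. For the secondary outcomes it refers back to model components that the text has not given. On reporting it says: "The results from the trial will be presented as regression coefficients for predicting change in primary and secondary outcomes with 95% confidence intervals".

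Section 2.3 adds two facts. The order is fixed: "Patients will be randomised once baseline data have been collected". And the allocation sequence is generated without restrictions, so nothing in the design balances baseline SF-36 between the arms.

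**The concern.** There are two linked points.

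**The baseline tests answer no question.** Allocation is by a concealed random sequence, so the null hypothesis of such a test is true by construction. A small p-value identifies a chance event. A large one does not show that an imbalance in a prognostic score is harmless. The section does not say what follows a significant result.

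**The wording leans towards change, and no adjustment is named.** If the LMEM takes baseline as one of the repeated outcomes, with a separate baseline mean in each arm, its arm-by-time contrast with complete data is the difference in mean change. That estimator subtracts the whole chance gap at baseline, although only a fraction rho of it is expected to persist to follow-up. Conditioning on the baseline score subtracts the right fraction and has smaller variance. The data needed are in hand for every patient before allocation.

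At stake is precision, not validity.

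**Working it through.** **Inputs from section 2.2.** The target is a 20-point difference between arms on the SF-36 physical scale. The spread is given in these words: "with a standard deviation (SD) between the groups of 36.16". The article does not say whether this is the SD of a single score or of change. Error rate, power and size come together: "an alpha value of 0.05 and a power of 80%, 53 subjects per group will need to be recruited".

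**Assumed.** The baseline to follow-up correlation rho is not in the article; 0.3, 0.5 and 0.7 are used. Variances are equal at both visits, tests are two-sided, data are complete, and there is one follow-up visit.

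**Step 1: reproduce the planned size.** The normal formula gives n = 2 × [36.16 × (1.960 + 0.842)/20]² = 51.3, so 52 per arm. With the t distribution, 52 per arm gives 79.8% power and 53 gives 80.5%, which matches the stated 53. The calculation is an unadjusted comparison of two means with no correlation term, so it takes no credit for baseline adjustment.

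**Step 2: variance ratio.** With single-score SD σ:
- SD of change = σ√(2(1−rho))
- SD after baseline adjustment = σ√(1−rho²)
- variance ratio, adjusted to change = (1−rho²)/(2(1−rho)) = (1+rho)/2

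This is below 1 for every rho below 1: 0.65, 0.75 and 0.85 at rho 0.3, 0.5 and 0.7.

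**Step 3: power at 53 per arm if 36.16 is a single-score SD** (noncentral t).

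| rho | SD change | SD adjusted | Power, change (0.05) | Power, adjusted (0.05) |
|---|---|---|---|---|
| 0.3 | 42.79 | 34.49 | 66% | 84% |
| 0.5 | 36.16 | 31.32 | 81% | 90% |
| 0.7 | 28.01 | 25.82 | 95% | 98% |

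A simulation with 53 per arm agreed. Standard errors were 7.0 (change) and 6.0 (adjusted) at rho 0.5, and 5.5 and 5.1 at rho 0.7. Both estimators were centred on the true 20 points.

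**Step 4: the other reading.** If 36.16 is the SD of change, the adjusted SD is 36.16 × √((1+rho)/2) = 29.15, 31.32 and 33.34. Power for change is then 81% at every rho, and adjustment raises it to 94%, 90% and 86%. The direction is the same, but the gain at a given rho is not.

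**Step 5: how large a chance gap could be.** On the single-score reading, the standard error of the difference in baseline means is 36.16 × √(2/53) = 7.02, so gaps of up to 1.96 × 7.02 = 13.8 points lie within the 95% range, against a 20-point target. For a 10-point gap at rho 0.5, a change analysis removes 10 points where 5 are expected to persist.

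**Step 6: the baseline tests.** Tables and text list 6 sociodemographic variables, 8 SF-36 dimensions, 5 cognitive and functional tests, 2 HADS scores, and one score each for insomnia, physical activity, self-efficacy, health literacy and activation: 6 + 8 + 5 + 2 + 5 = 26, before symptom severities. If all were tested at 0.05 (the article states no level for these tests), 26 × 0.05 = 1.3 significant results would be expected by chance.

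**The case against.** The strongest objection is that the model attacked is not stated. The article lists no LMEM terms, and an article commonly leaves these to the full protocol or SAP. Coefficients for change are also compatible with adjustment: regressing change on arm and baseline gives the same arm coefficient as regressing the follow-up score on arm and baseline. An LMEM with a common baseline mean is likewise equivalent. In either case the remedy is already in place and no power is lost. All of this stands.

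A reader might therefore infer too much in four ways:
- **That the plan fails to adjust for baseline.** The article does not establish this; it only names no adjustment.
- **That a power loss has been shown.** The power figures rest on an assumed rho, on one reading of 36.16, and on a two-visit complete-data approximation to a plan with two post-baseline visits. On the single-score reading, change already reaches the planned 80% at rho 0.5.
- **That a change contrast is biased.** Under randomisation it is not.
- **That the baseline tests will steer covariate choice.** No such rule is written; the section is silent on what follows.

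The LMEMs are to be tested at 0.01 while the trial is sized at 0.05. That mismatch is a separate matter, and its cost in power should not be attributed to the handling of baseline.

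What the objection leaves untouched: the baseline tests are an explicit procedure, not a gap that another document could fill, and they are the only handling of baseline that section 2.7 describes.

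**Conclusion.** The point holds as an efficiency improvement and a correction of uninformative tests, not as an error that invalidates the analysis. The statement about the tests is unconditional. The statement about precision is conditional: if the LMEM is an arm-by-time contrast with free baseline means, adjusting for baseline cuts the variance to (1+rho)/2 of its value, assuming equal variances. On the single-score reading at alpha 0.05 that is worth about 18, 10 and 2 percentage points of power at rho 0.3, 0.5 and 0.7. On the SD-of-change reading it is about 13, 10 and 6 points. Adjustment corrects for chance imbalance in the measured baseline score only, not in other prognostic factors, and the variance gain shrinks as rho approaches 1.

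**What to change.** In section 2.7:
1. Delete the ANOVA and chi-square tests of baseline differences and keep the descriptive baseline table by arm.
2. State the model: an LMEM for the end-of-intervention and 3-month scores, with that outcome's baseline value, arm, visit and arm-by-visit as fixed effects and a patient random effect. An equivalent choice keeps baseline among the repeated outcomes and constrains its mean to be equal across arms.
3. State that this model is fitted whatever the baseline table shows, and that the secondary scores use the same form.

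The cost is a few sentences. No new data, visits or patients are needed. If the full protocol or SAP already specifies such a model, only the tests need to go and the article's wording be aligned.

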#### Primary outcome

2.6.1.

The main variable will be quality of life, evaluated through the SF-36 (67). This questionnaire measures eight dimensions of health: physical function, physical role, aches and pains, general health, vitality, social function, emotional role and mental health; it also includes a declared health evolution item. The eight dimensions define two main components of health: a physical summary component and a mental summary component. In them, scores above or below 50 indicate, respectively, a better or worse state of health than the mean of the reference population. Items are scored on a Likert-type scale from 1 to 3.5 or 6, depending on the type of item. The total score of the eight scales ranges from 0 to 100, with higher scores indicating better health. The validated Spanish version of the questionnaire will be used (68).

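### The 0.01 test level (0.05/5) matches no count of tests in the article and contradicts a sample size planned at 0.05, so the physical scale has about 59–66% power, not 80%, unless baseline adjustment makes up the difference

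*Protocol article*

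**What the plan says.** Section 2.6.1 (Primary outcome) names an instrument, not a score: "The main variable will be quality of life, evaluated through the SF-36 (67"). It adds that "This questionnaire measures eight dimensions of health", and that "The eight dimensions define two main components of health: a physical summary component and a mental summary component". The eight scales are given a range of 0 to 100. For the components, "scores above or below 50 indicate, respectively, a better or worse state of health than the mean of the reference population".

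Section 2.2 (Patient inclusion and sample size) plans "to detect a mean difference of 20 points on the physical scale of the 36-Item Short Form Health Survey Questionnaire (SF-36"), with SD 36.16, alpha 0.05 and 80% power, giving 53 per group. A second calculation for a mental scale, with the same difference, alpha and power and SD 29.99, gives 35 per group. The larger figure plus 10% gives 116 in total.

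Section 2.7 (Statistical analysis) uses linear mixed-effects models for the primary outcome and the same models for the secondary variables. It then sets the level: "LMEMs will be tested against a Bonferroni-adjusted alpha level of 0.01 (0.05/5"). Results "will be presented as regression coefficients for predicting change in primary and secondary outcomes with 95% confidence intervals".

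**The concern.** Two statements in the article do not fit together. Section 2.2 sizes the trial for tests at 0.05, and section 2.7 carries them out at 0.01. A stricter test on the same sample has less power, so the stated 80% cannot be carried over to the stated test without some further gain in precision that the article does not claim.

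The divisor of 5 also has no visible source. The article offers two components, eight scales, or two planning scales, and none of these is five. Without knowing which tests share the 0.05, a reader cannot say what overall error rate the main claim carries, or whether 0.01 is too strict or too lenient for it. At stake are whether a true 20-point effect would be declared, and which SF-36 result would count as the trial's answer.

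**Working it through.** **Inputs.** From section 2.2: difference 20; SD 36.16 (physical) and 29.99 (mental); alpha 0.05; power 80%; 53 and 35 per group; 58 per group after the allowance for losses. From section 2.7: alpha 0.01 = 0.05/5. Assumptions: equal allocation and two-sided tests. Sidedness is not stated, but one-sided 0.05 would give 41 and 28 per group, which does not match the plan.

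**1. Reproduce the plan.** n per group = 2 × [SD × (z for 1 − alpha/2 + z for power) / difference]².
- Physical: 2 × [36.16 × (1.960 + 0.842)/20]² = 51.3, so 52. Using the t distribution instead gives 53, as stated.
- Mental: 2 × [29.99 × 2.802/20]² = 35.3, so 36 (stated 35).
- Losses: 106 × 1.10 = 116.6, stated as 116.

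The planned figures therefore reproduce at alpha 0.05, to within one subject per group.

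**2. Power at the level that will be used.** Signal = 20 / [SD × √(2/n)]. For the physical scale this is 2.847 with 53 per arm and 2.979 with 58. In the normal approximation, power at 0.01 is Φ(2.847 − 2.576) = Φ(0.271) = 0.607 with 53, and Φ(0.403) = 0.656 with 58. The t-test figures are slightly lower.

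| Scale | n per arm | alpha 0.05 | alpha 0.025 | alpha 0.01 |
|---|---|---|---|---|
| Physical | 53 | 0.805 (t), 0.813 (normal) | 0.716, 0.728 | 0.589, 0.607 |
| Physical | 58 | 0.840, 0.846 | 0.759, 0.769 | 0.640, 0.656 |
| Mental | 53 | 0.925, 0.930 | 0.875, 0.883 | 0.789, 0.804 |
| Mental | 58 | 0.945, 0.949 | 0.905, 0.911 | 0.832, 0.845 |

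The mental scale keeps about 80% at 0.01 because the physical scale sets the sample size. The physical scale does not.

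**3. Sample size that 0.01 would need.** Physical: 2 × [36.16 × (2.576 + 0.842)/20]² = 76.4, so 77 per group (154) before losses, against the planned 53 (106).

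**4. Effect of using baseline.** If the model uses baseline, the SD shrinks by √(1 − r²), where r is the correlation between baseline and follow-up. The article gives no r, so a range is shown. Physical-scale power at 0.01 (t) is:

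| r | 53 per arm | 58 per arm |
|---|---|---|
| 0 | 0.59 | 0.64 |
| 0.3 | 0.64 | 0.69 |
| 0.5 | 0.75 | 0.79 |
| 0.6 | 0.82 | 0.86 |

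**5. Error rate for the main claim.** With k tests at 0.01, the family-wise error is at most k × 0.01: 0.02 for two scores, 0.05 for five, 0.08 for eight and 0.10 for ten. Bonferroni levels for 2, 8 and 10 tests would be 0.025, 0.00625 and 0.005. None of them is 0.01.

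**6. Metric.** The planned effects are 20/36.16 = 0.55 SD and 20/29.99 = 0.67 SD. If the components had a reference SD of 10 (an assumption; the article gives none), 20 points would be 2 SD. An SD of 36.16 also exceeds that of a uniform spread over 0 to 100 (100/√12 = 28.9). The planning figures look more like one of the 0–100 scales than a component centred on 50, but this is an inference.

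**The case against.** The strongest reply is that this is a condensed article. The list of tests, the exact score and the primary visit may stand in an analysis plan that is not shown, and their absence here is then no fault. That is right as far as it goes: it cannot be said that no family of five exists, only that the article names none. It does not answer the conflict between sections 2.2 and 2.7, which both state an alpha and state different ones.

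A second reply is that a mixed model with baseline will be more precise than the two-sample comparison used above. This also stands in part. With r around 0.6, power at 0.01 returns to about 80%. But section 2.2 does not rely on this gain and gives no correlation.

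Three stronger readings are tempting and should not be drawn.
- A reader might count ten SF-36 scores at two visits and infer a family-wise error of up to 20 × 0.01 = 0.20. Nothing in the article says that twenty contrasts are tested separately or that any one of them would count as success. Section 2.2 points instead to two scores, for which 0.01 is conservative.
- A reader might take 95% intervals beside a 0.01 test as an error-rate problem. At the design effect with 53 per arm, p falls between 0.01 and 0.05 in about 0.805 − 0.589 = 22% of trials, and interval and test would then seem to disagree. The intervals are not the decision rule, so this is a matter of presentation and does not change the type I error.
- A reader might conclude that SD 36.16 cannot belong to a summary component. No reference SD is given, the source of the SDs is not at hand, and section 2.6.1 itself supplies a 0–100 metric to which the figures could belong.

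**Conclusion.** The point holds in a limited form. The per-test level is clearly fixed at 0.01, but the five tests behind it are not identified, and it contradicts the 0.05 on which the sample size rests. For the physical scale, which determines the sample size, the stated 80% becomes about 59–61% with 53 per arm and 64–66% if all 58 are retained. This assumes two-sided tests, the planned SD and an unadjusted comparison of two means; power is higher if the model uses baseline.

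The direction of any error-rate problem is not established. The family-wise error is at most 0.02 if two scores carry the claim, and its bound passes 0.05 only if more than five tests can support it. On the plan's own sizing, the likelier harm is lost power. The uncertainty about the planning metric is secondary, but it should be cleared up at the same time.

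**What to change.** Make these changes before any outcome is compared by group:
- **Section 2.6.1:** name the physical and mental SF-36 scores on which section 2.2 was sized, and one primary time point.
- **Section 2.7, primary claim:** replace 0.05/5 with a fixed sequence of the two scores at 0.05, with the order stated. With the physical score first, that test keeps the planned 80% and no larger sample is needed. If 0.025 each or 0.01 is preferred, restate physical-scale power as about 72% or 59% with 53 per arm.
- **Section 2.7, other results:** treat the remaining SF-36 scores, the other visit and all other outcomes as supportive. Give the primary intervals at the level of their test.
- **Section 2.2:** state which score and which metric the 20 points and the SDs refer to.

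The fixed sequence costs wording only, but the second score can be tested formally only if the first succeeds. The other SF-36 scores lose any primary status. The change must be notified to the ethics committee, as the ethics section provides for any modification. With 90 of 116 participants already recruited at the time of writing, it should be made and dated soon.

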## Discussion

3.

The number of people with long COVID, most of them young and without previous pathologies, continues to increase. However, due to the limited scientific evidence, this pathology is still largely unknown in primary care, and patients still find it difficult to receive recognition, support, medical evaluation and treatment for this condition (90, 91).

There is no standard protocol for the treatment of long COVID. Programmes are being designed with the aim of improving the physical health and mental well-being of these patients; however, some key points such as the content of these programmes, the method of offering them and their duration, among other factors, are still being investigated. These programmes include pharmacological treatments and other approaches such as pulmonary and cardiac rehabilitation, fatigue treatment, etc. These types of disease management are primarily directed at symptom control (92).

Long COVID is considered a multisystem syndrome, and > 100 different symptoms—general, physical, respiratory, cognitive, psychological, etc.—have been reported. Hence, the treatment approach requires an interdisciplinary vision that includes, among others, physical rehabilitation, cognitive rehabilitation, respiratory physiotherapy and psychological intervention, and whose objective is to recover the functional state prior to the disease. In addition, due to the heterogeneity of each case, rehabilitation programmes must be personalised (1, 93).

In recent years, especially during the COVID-19 pandemic when face-to-face contact was limited, the use of digital technology has optimised traditional medical care, improving safety, efficacy and adherence to treatments (94).

The evidence supports the use of digital interventions, highlighting their potential in the control of persistent physical and psychological symptoms of COVID-19, and improving the quality of life of people with these symptoms (9, 28, 95–98). However, Rinn et al., in their scoping review, state that research is still needed on individualized digital interventions that better suit the requirements of these patients (99).

To the best of our knowledge, this is the first randomised controlled trial that will be carried out with the objective of analysing the effectiveness of an interdisciplinary and online multimodal intervention, through videoconferences, in addressing the symptoms of people with Long COVID and in improving their quality of life.

This project has strengths and limitations. Among the strengths are that its national and remote character through videoconferences will offer people with long COVID the opportunity to expand their support network and to learn about similar experiences and resources offered in other communities. The online platform used for support will give the patients access to all of the content, and the videoconferences will promote adherence to the programme, as well as the personalisation of the therapeutic recommendations offered in it. Among the limitations of the study are possible technological barriers as well as the lack of knowledge and skills related to information and communication technologies by some users. Another limitation may be the possible dropout of study participants, which might happen due to reinfections that cause their health status to worsen, or to the search for other face-to-face, individualised and more personalised health care resources during the study. Nonetheless, the reasons for dropout and other problems that may arise throughout the research project will be collected by the researchers in accordance with the Mechanisms of Action in Group-based Intervention (MAGI) framework (100).

